**Dangerous**	Patients have to meet one of the conditions below: 1. INR is < 1.5 or > 4.5 2. Patients have major bleeding 3. Patients have thrombosis 4. Patients have other severe symptoms, such as dyspnea, severe headache	The health care providers will call the patients immediately. Patients will be advised to go to the local hospital or tertiary hospital for further treatment based on their risks.

#### Control patients

Patients will receive the warfarin education courses the same as the SMART model group after they sign the informed contents as mentioned above. However, we will not intervene the warfarin manage mode in the control groups.

#### Follow-up visits and data collection

Each of the enrolled patients has to record his/her warfarin related information in a printed monitoring handbook, including INR results, warfarin dosage, other medicine, diet change, new disease, and thrombosis or bleeding events (if occurs). All the patients are required to receive follow-ups at the 3rd, 6th, 9th and 12th month through outpatient clinic visits, telephone or online interviews. At each follow-up time-point, the research stuff will collect the warfarin related information. Double data entry will be carried out to ensure data accuracy and data will be kept in encrypted mobile hard disks to protect patients’ privacy. Only the corresponding author has access to the final trial dataset. As shown in Table 3, patients are required to provide the information of warfarin dosage and INR results, the numbers of going to the outpatient clinics or inpatient treatment due to warfarin, quality of life as measured by the health index scale (EQ-5D-3L) [16], and the related treatment costs. At baseline and the last time visit, patients are required to fill in the Morisky anticoagulant compliance questionnaire [14] and the oral anticoagulation knowledge test [15]. An anticoagulation satisfaction survey by using the Duke Anticoagulation Satisfaction Scale [17] will be conducted to all the patients at the end of the study. The research staff will send text messages to remind the patients for follow-ups and all the participated patients will receive certain amount of compensation fees to sustain their involvement in the study.

**Table 3 Tab3:** Measurement domains, survey methods and collection time-points

Variable	Component	Measurement methods	Baseline	3rd M	6th M	9th M	12th M
**Socio-demographic parameters**	Gender, age, telephone, address, education, occupation and annual income	Face-to-face interview	√				
**Clinical parameters**	Height, weight, warfarin indication, start date of warfarin, warfarin dosage, TTR calculated by INR tests in the preceding 12 months, history of thrombosis or major bleeding, concomitant diseases and medicine Warfarin dosage, INR, bleeding or thrombosis, other clinical adverse events	Face-to-face interview	√				
		Face-to-face interview, telephone or online interview		√	√	√	√
**Behaviour parameters**	Anticoagulant compliance, warfarin knowledge,	Morisky Anticoagulant Compliance Questionnaire [14], Oral Anticoagulation Knowledge (OAK) Test [15]	√				√
	Treatment behavior, quality of life	Self-made questionnaire, EQ-5D-3L Form [16]	√	√	√	√	√
	Anticoagulation satisfaction	Duke Anticoagulation Satisfaction Scale [17]					√
**Economic parameters**	Direct costs (INR test fees, outpatient clinic visit fees, hospitalization or emergency room visit fees if occurs), Indirect costs (deducted income due to absence of working, traffic and accommodation fees)	Face-to-face interview, telephone or online interview	√	√	√	√	√

### Outcomes

#### Primary outcome measure

The difference in TTR between the SMART model group and the control group during the 12 month period of study.

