**Methods:**

This is a multi-center randomized controlled trial. We will carry out the study in three county hospitals, three small tertiary hospitals and three large tertiary hospitals with anticoagulation clinics in Hunan province of China. Eligible patients will be randomly assigned to the SMART model group (*n* = 360) or the control group (usual care clinic group, *n* = 360; anticoagulation clinic group, *n* = 120). Patients in the SMART model group do PST at home once every two to 4 weeks. Controls receive usual care in the clinics. All the patients will be followed up through outpatient clinics, phone call or online interviews at the 3rd, 6th, 9th and 12th month. The percentage of time in therapeutic range (TTR), incidence of warfarin associated major bleeding and thromboembolic events and costs will be compared between the SMART model group and control groups.

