In China, the percentage of time in therapeutic range (TTR, a tool of measuring warfarin treatment effects) was less than 40%, which was significantly lower than that of 62% in western countries [4]. Clinical observation studies found that warfarin associated ischemic stroke and intracranial bleeding were respectively 5.23 and 2.94% in patients from China, significantly higher than patients from the rest of the world (2.94 and 0.63%, respectively) [5]. In warfarin-treated patients in China, the median in-hospital direct cost per patient was about $3, 000 for thrombosis and $4, 500 for intracranial hemorrhage [6]. These data suggest that warfarin management in China needs further improvement. An investigation study launched by the PI using the Andersen’s Health Services Utilization Behavioral Model in 469 patients on warfarin indicated that long time and high cost for travel, low family income, low quality of warfarin monitoring and dosing in local hospitals were dominant reasons for missing follow-ups (data not published yet).

Anticoagulation clinics (AC) have been proved safer and more effective than usual care in warfarin management [7, 8], but there are only about 50 ACs located in big cities of China (mainly run in a physician-pharmacist cooperative AC pattern) at present. The number of ACs is too low, and it is not easy to open more ACs due to limitation of health care professionals and longtime education.

Point-of-care testing (POCT) device designed for measuring INR by patients or their families was first developed in 1980s in America [9] and then widely used in many developed countries. Compared to traditional laboratory INR test in outpatient clinics, POCT has great advantages in convenient home testing and fast result reporting. Soon patient self-testing (PST) for warfarin home management by using POCT devices and telehealth has been rapidly applied in developed countries. Although the PST model of warfarin management has demonstrated improvement of clinical outcomes compared to usual care clinics and anticoagulation clinics [10], it is rarely applied in developing countries, including China.

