## Methods/design

### Study design

This is a multi-center randomized controlled trial. We will carry out the study in three large tertiary hospitals with anticoagulation clinics, three small tertiary hospitals and three county hospitals in Hunan province of China. Eligible patients will be randomly assigned to the SMART model group or the control group (usual care clinic and anticoagulation clinic). Patients in the SMART model group do PST at home once every two to 4 weeks. Control patients receive usual care without intervention. All the patients will be followed up through outpatient clinics, phone call or online interviews at the 3rd, 6th, 9th and 12th month. The percentage of time in therapeutic range (TTR), incidence of warfarin associated major bleeding and thromboembolic events and costs will be compared between the SMART model group and control groups. Figure 1 describes the study design.

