### Study settings

As the quality of medical care in China is unbalanced distributed, we will carry out the study in hospitals respectively representing low (county hospitals), medium (small tertiary hospitals) and high levels (big tertiary hospitals with ACs) of anticoagulation management in Hunan province to comprehensively evaluate the SMART model. Three hospitals of each level are randomly selected, thus finally nine hospitals are included in this study. Our hypothesis is that the SMART model is not only better than the usual care (UC, physician managed clinics) and the AC management, but also could be applied in different levels of hospitals in China.

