#### Randomization

In low and medium level hospitals, only the UC group is used as the control group, thus eligible patients on warfarin will be randomly assigned to either the SMART model group or the UC group. While in the high level hospitals, both AC and UC are used as the control groups, thus eligible patients will be randomly allocated to the SMART model group, the AC group or the UC group. For each level of the three hospitals, a total of 120 patients in each arm will be enrolled. The flow chart of patients’ grouping and allocation is shown in Fig. 2. Patients’ randomization will be carried out by research staff using a standard protocol available in the website (http://stattrek.com/statistics/random-number-generator.aspx).

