#### Data analyses

We will report continuous variables as means ± SD and categorical variables as proportions. Data will be checked for normal distribution by means of the Kolmogorov–Smirnov’s test. In compliance with the distribution of data, Student’s t-test or Mann–Whitney’s U-test will be used for comparisons between the SMART model group and control group. Chi-square or Fisher’s exact tests will be used to compare between the SMART model group and control group with respect to categorical data. The control of anticoagulation will be assessed by evaluating TTR with the Rosendaal method [18] in each arm. The follow-up assessment data will be analyzed using Generalized Linear Mixed Model and survival analysis. *P* ≤ 0.05 is considered statistically significant. All tests are two tailed. From the perspective of health-care payer, we will conduct a cost-effectiveness analysis to assess the economic impact of the SMART model for warfarin home management. A Markov model, a half-cycle correction and a discount of 5% will be constructed or used to estimate the total costs and quality-adjusted life-years (QALYs) over the 2-year period (the outcomes beyond the observation period will be predicted according to the results obtained in the study). We will collect the direct and indirect costs of each enrolled patient on warfarin, evaluate their quality of life through EQ-5D-3L utility value from data provided by patients, calculate QALYs, and analyze the effects of multiple variables by the Linear Mixed Effects Model. The direct costs include laboratory INR test fees in the control groups (or POCT fees in the SMART model group), outpatient clinic visit fees (or supervision fees in the SMART model group), hospitalization fees and emergency room visit fees. The indirect costs include deducted income due to absence of working, traffic fees and accommodation fees. Because warfarin is very cheap, the medication fee of warfarin is not calculated in each group. The incremental cost effectiveness ratio (ICER) will be calculated according to the total costs and QALYs, and one-way and probabilistic analyses will be performed to verify the stability of the model.

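### The article's primary contrast sets SMART against a control group made up of UC and AC, but AC exists only in high-level hospitals: the unadjusted test is confounded by hospital level and matches neither stated hypothesis

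*Protocol article*

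**What the plan says.** Primary outcome measure: "The difference in TTR between the SMART model group and the control group during the 12 month period of study". The control group is one entity with two components. Study design states: "Eligible patients will be randomly assigned to the SMART model group or the control group (usual care clinic and anticoagulation clinic". The abstract's Methods paragraph gives the sizes: "or the control group (usual care clinic group, *n* = 360; anticoagulation clinic group, *n* = 120". Data analyses says that the t-test or Mann-Whitney test "will be used for comparisons between the SMART model group and control group", and Sample size determination uses the same two-group contrast with a 5% difference in TTR.

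Randomization shows that the two controls are not spread evenly. "In low and medium level hospitals, only the UC group is used as the control group", whereas "in the high level hospitals, both AC and UC are used as the control groups". Each arm has 120 patients per hospital level.

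Study settings selects hospitals to represent low, medium and high levels of anticoagulation management, and names two comparators: "Our hypothesis is that the SMART model is not only better than the usual care (UC, physician managed clinics) and the AC management". Background says that anticoagulation clinics "have been proved safer and more effective than usual care in warfarin management".

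Two passages point the other way. The abstract and Study design also say that outcomes will be compared between SMART and the control groups, in the plural. Data analyses also names a generalized linear mixed model for the follow-up data, without terms or contrast.

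**The concern.** Randomisation protects comparisons within a hospital level. It protects a comparison pooled over levels only if the allocation ratio is the same at each level or the analysis accounts for level. With UC and AC combined, SMART to control is 1:1 at the low and medium levels and 1:2 at the high level, so a crude comparison gives high-level hospitals more weight among controls than in SMART. If TTR is better in those hospitals, as Study settings implies, the crude difference is pushed below zero when SMART has no effect.

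There is a second, separate problem. Even without confounding, a blend of UC and AC answers neither half of the hypothesis. A benefit over UC and a deficit against AC can cancel.

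At stake is the primary result: a real benefit over usual care could be missed, and the article's claims about each comparator would go untested.

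**Working it through.** **Inputs from the article.** 120 patients per arm per level; SMART and UC at all three levels; AC at the high level only; target difference 5 points; two-sided 5% test; 31 per group before dropout.

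**Inputs assumed.** Mean TTR under UC at the low, medium and high levels (mL, mM, mH); a = AC minus UC within the high level; within-level SD of TTR. The article gives none of these.

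**1. The article's own totals.** SMART 3 × 120 = 360; UC 3 × 120 = 360; AC 1 × 120 = 120. These match the abstract. Combined control = 360 + 120 = 480.

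**2. Level mix.**

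| | Low | Medium | High | High-level share |
|---|---|---|---|---|
| SMART | 120 | 120 | 120 | 120/360 = 33% |
| UC + AC | 120 | 120 | 240 | 240/480 = 50% |
| UC alone | 120 | 120 | 120 | 120/360 = 33% |

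The imbalance comes only from adding AC; SMART and UC are balanced at every level.

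**3. Shift in the crude mean difference when SMART equals UC at each level.**

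- SMART mean = (mL + mM + mH)/3
- Combined control mean = (mL + mM + 2mH + a)/4
- Difference = (mL + mM − 2mH)/12 − a/4

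The first term is confounding by level. The second is a change of estimand: a real AC-UC difference entering the comparator.

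- Means 40/45/50%: (40 + 45 − 100)/12 = −1.25 points
- Means 40/50/60%: (40 + 50 − 120)/12 = −2.5 points
- If a = 5, the estimand term adds −5/4 = −1.25 points in either case

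**4. Effect on the crude t-test, means 40/50/60%, a = 0.** With a true gain of 5 at every level, the expected crude difference is 5 − 2.5 = 2.5. The test's SE includes the between-level spread, whose pooled variance is 57,000/840 = 67.9. The actual sampling SE uses only the within-level SD, because the stratum sizes are fixed.

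At SD 20:

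- Test SE = √[(400 + 67.9)(1/360 + 1/480)] = 1.508
- Rejection threshold = 1.963 × 1.508 = 2.96
- Sampling SE = 20 × √(1/360 + 1/480) = 1.394
- Power = Φ[(2.5 − 2.96)/1.394] = 0.37

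| SD | Power, true gain 5 | Rejection rate, no effect (against SMART) |
|---|---|---|
| 7 | 0.98 | 0.98 |
| 15 | 0.56 | 0.56 |
| 20 | 0.37 | 0.37 |

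The two columns agree because the expected differences are +2.5 and −2.5 with the same variance. A simulation of 4,000 trials per SD with no true effect gave rejection rates of 0.98, 0.55 and 0.36 for the crude test, and 0.053, 0.048 and 0.048 with a level term added.

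The SD range starts at 7 because 31 per group implies it: 5/[(1.960 + 0.842) × √(2/31)] = 7.0.

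**5. Cancellation.** Keep means 40/50/60%, let SMART beat UC by 5 at every level, and let AC beat UC by 10. SMART is then 5 below AC. The crude difference is 5 − 2.5 − 10/4 = 0.0.

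**6. Power for 5 points if the contrasts are separated.**

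| SD | SMART vs UC, 360 vs 360 | SMART vs AC, 120 vs 120 |
|---|---|---|
| 7 | >0.99 | >0.99 |
| 15 | 0.99 | 0.73 |
| 20 | 0.92 | 0.49 |

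**The case against.** The strongest reply is that a pooled test is inferred. No sentence says outright that UC and AC will be merged for the primary test. The plural form appears in several places, Data analyses computes TTR in each arm, and the Discussion uses the singular while talking about differences within hospital level, so the singular may be generic. The t-test sentence is general, the mixed model could carry a hospital term, and model terms are commonly left to an analysis plan that is not shown.

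Much of this stands. A reader might infer that the sponsor has committed irrevocably to a crude 360 versus 480 test; the documents do not go that far. But the article does define the control group as UC plus AC and uses that single group in the primary outcome, the two-group tests and the sample size. It states no separate SMART-UC or SMART-AC primary contrast, and the mixed model has no stated level term or contrast that would settle the matter. The finding is a stated contrast that conflicts with the allocation and the hypothesis; missing model detail alone would not be one.

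The objections to size also stand in part. At the SD of about 7 implied by the sample size, power at 40/50/60% is still 0.98, so a collapse in power cannot be asserted without assuming a larger SD. Background's TTR figures of below 40% and 62% contrast China with western countries; a reader might take them for a spread between hospital levels, but the article gives no TTR by level. Nor should the whole shift be called confounding, since the −a/4 part is a real difference between comparators.

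Finally, if high-level hospitals have better TTR, the bias runs against SMART. A reader might fear a false claim of benefit; for TTR the likelier error is a missed benefit or an apparent deficit.

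**Conclusion.** The concern holds. Followed as written, the primary comparison is confounded by hospital level and tests neither stated hypothesis. The 33% versus 50% imbalance and the mismatch with the hypothesis follow from the article's own numbers and wording and need no assumption.

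The size does rest on assumptions: a confounding shift of −1.25 points at 40/45/50% and −2.5 at 40/50/60%, against a 5-point target, plus a separate −a/4 if AC differs from UC. The power and error rates also assume a uniform 5-point effect, although the Discussion expects the largest TTR difference in county hospitals. They apply to the t-test; the Mann-Whitney test faces the same imbalance but was not calculated.

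The randomised design itself is sound. SMART versus UC is balanced at every level, and SMART versus AC is randomised within the high-level hospitals, so the right contrasts are available from the data already planned.

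**What to change.** State the primary contrast as SMART versus UC across all nine hospitals (360 versus 360), adjusted or stratified by hospital. State SMART versus AC as a separate contrast within the three high-level hospitals only (120 versus 120), adjusted by hospital. Comparing all 360 SMART patients with the 120 AC patients would bring the confounding back.

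Add a multiplicity rule in advance. Fixed order, UC then AC, is one acceptable choice among several. Drop the combined UC plus AC test, and use the same structure for the secondary outcomes.

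The cost is a wording change in the protocol or analysis plan and one model, with no added patients or data. Recruitment began in March 2021, so the change should be dated before any outcome is compared by arm. The downside is that the AC contrast then openly rests on 120 versus 120, and its power may be limited, as the last table in the working shows.

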#### Secondary outcome measures

The numbers of INR results indicating excessive under-coagulation or over-anticoagulation (INR < 1.5 or INR > 5.0).Serious adverse clinical events (clinical relevant non-major bleeding, major bleeding, thrombosis or death)Patients’ quality of life.Costs on warfarin management.

#### Data monitoring

As the corresponding author is the principle investigator and the Xiangya Second Hospital of Central South University is the coordinating center of the study, the Clinical Research Ethics Committee of Xiangya Second Hospital of Central South University has reviewed and approved this study protocol (Protocol version: XY2-POCT01). The committee monitors all human research conducted by stuff in the Xiangya Second Hospital, which is independent from the sponsor and competing interests. The three participated county hospitals do not have clinical research ethics committee, so they accept the ethical approval from Xiangya Second Hospital of Central South University. For the other five participated tertiary hospitals, their clinical research ethics committee will approve the study independently. We will seek approval from the clinical research ethics committee of the participated hospital for any important procedure modifications and inform patients according to their guidelines. We have registered the study in Chinese Clinical Trial Registry (No.ChiCTR2000038984). The research staff will report adverse events and other unintended effects of the trial intervention to the Ethics Committee and manage these events according to their guidelines.

#### Data analyses

We will report continuous variables as means ± SD and categorical variables as proportions. Data will be checked for normal distribution by means of the Kolmogorov–Smirnov’s test. In compliance with the distribution of data, Student’s t-test or Mann–Whitney’s U-test will be used for comparisons between the SMART model group and control group. Chi-square or Fisher’s exact tests will be used to compare between the SMART model group and control group with respect to categorical data. The control of anticoagulation will be assessed by evaluating TTR with the Rosendaal method [18] in each arm. The follow-up assessment data will be analyzed using Generalized Linear Mixed Model and survival analysis. *P* ≤ 0.05 is considered statistically significant. All tests are two tailed. From the perspective of health-care payer, we will conduct a cost-effectiveness analysis to assess the economic impact of the SMART model for warfarin home management. A Markov model, a half-cycle correction and a discount of 5% will be constructed or used to estimate the total costs and quality-adjusted life-years (QALYs) over the 2-year period (the outcomes beyond the observation period will be predicted according to the results obtained in the study). We will collect the direct and indirect costs of each enrolled patient on warfarin, evaluate their quality of life through EQ-5D-3L utility value from data provided by patients, calculate QALYs, and analyze the effects of multiple variables by the Linear Mixed Effects Model. The direct costs include laboratory INR test fees in the control groups (or POCT fees in the SMART model group), outpatient clinic visit fees (or supervision fees in the SMART model group), hospitalization fees and emergency room visit fees. The indirect costs include deducted income due to absence of working, traffic fees and accommodation fees. Because warfarin is very cheap, the medication fee of warfarin is not calculated in each group. The incremental cost effectiveness ratio (ICER) will be calculated according to the total costs and QALYs, and one-way and probabilistic analyses will be performed to verify the stability of the model.

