#### Baseline interview

All the participated patients will be required to complete a survey either via an online survey through their mobile phone or via a printed brochure. The contents of the survey contain three parts, including patients’ clinical parameters (warfarin indication, start date of warfarin, warfarin dosage, previous TTR, history of thrombosis or major bleeding, concomitant diseases and medicine), behaviour indicators (warfarin knowledge, anticoagulant compliance, treatment behavior and quality of life) and costs on warfarin related treatment.

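### The primary TTR comparison is picked by a normality pre-test, so its effect measure depends on the data, and neither candidate test uses baseline TTR or hospital

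*Protocol article*

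**What the plan says.** The Primary outcome measure section defines the endpoint as "The difference in TTR between the SMART model group and the control group during the 12 month period of study". It does not say whether means, medians or ranks are compared.

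Under Data analyses, "Data will be checked for normal distribution by means of the Kolmogorov"–Smirnov test. Then, "In compliance with the distribution of data", either Student's t-test or Mann–Whitney's U-test "will be used for comparisons between the SMART model group and control group". No other two-group test is named for a continuous outcome. The section gives no level for the pre-test, no variant, and no rule on whether it is run by arm or on pooled data.

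The same section adds that "The follow-up assessment data will be analyzed using Generalized Linear Mixed Model and survival analysis". Response variables, covariates and the standing of that model (primary or supportive) are not given. The section also commits to reporting continuous variables as means with SDs.

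On baseline data, the Baseline interview section states that "All the participated patients will be required to complete a survey", and previous TTR is among its clinical items. Table 3 lists "TTR calculated by INR tests in the preceding 12 months".

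**The concern.** A t-test and a Mann–Whitney test answer different questions. The first concerns a difference in mean TTR, which is the natural reading of the 5% difference in the Sample size determination section. The second concerns whether a patient in one arm tends to rank above a patient in the other. If a pre-test on outcome data decides between them, the effect measure of the primary analysis is not fixed in advance.

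The pre-test is also a poor guide. Its power grows with sample size, so it is most likely to reject in large arms, where a comparison of means least needs normality.

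Both tests leave out two variables the trial will have. TTR over the preceding year is the obvious predictor of TTR over the next. Hospital matters because the Study settings section chose sites to represent three levels of anticoagulation quality, and the Randomization section offers different arms at different levels. If the two-group tests are the primary analysis, that information is not used.

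**Working it through.** **The plan's own figure.** The article gives 31 per group for 5 points, 80% power and two-sided 0.05, without an SD, so 31 cannot be reproduced, only back-solved. From n = 2·SD²·(1.960 + 0.842)²/5², SD = 5 / (2.802 × √(2/31)) = 7.03 (6.91 with the t distribution). Planned arms are larger: 120 per arm at each hospital level, giving 360 SMART, 360 usual care and 120 anticoagulation clinic.

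**Does the pre-test steer the analysis?** TTR is bounded between 0 and 100, so it was simulated as a beta variable with equal true means in two arms, 600 runs per scenario. The means and SDs are assumptions. The table shows how often normality was rejected in at least one arm at mean 60, SD 20 in both arms:

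| Patients per arm | K–S, uncorrected | K–S, Lilliefors correction |
|---|---|---|
| 34 | 0.2% | 18% |
| 120 | 0.5% | 42% |
| 360 | 16% | 94% |

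A third variant, the uncorrected test on all 840 patients pooled, rejected in 62% of trials for the same mean and SD. The article does not say which of these is meant, so the branch taken depends on arm size and variant.

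**Does the branch matter?**
- Equal distributions in both arms (mean 60, SD 20, 360 per arm): t-test 4.8% rejections, Mann–Whitney 5.0%, two-stage rule with Lilliefors 5.0%. There is no inflation.
- Equal means, unequal spread (mean 60, SD 15 versus 25, 360 per arm): t-test 5.0%, Mann–Whitney 16.5%, two-stage rule 16.8%. At 120 per arm: 5.2%, 9.5% and 9.5%.

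With 600 runs, the simulation error of 16.5% is √(0.165 × 0.835/600), or 1.5 percentage points. In the second case Mann–Whitney responds to a difference in shape when the mean difference is zero.

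**What would adjustment gain?** Adjusting for a baseline value that has correlation r with the outcome multiplies the residual variance by 1 − r². The article gives no r, so a range is assumed:
- r = 0.3: factor 0.91, equivalent to 1.10 times the patients
- r = 0.5: factor 0.75, equivalent to 1.33 times
- r = 0.6: factor 0.64, equivalent to 1.56 times

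**Power for 5 points, SMART versus anticoagulation clinic.** Allowing the planned 10% dropout, 120 × 0.9 = 108 per arm. By normal approximation, power = Φ(5 / (SD·√(1 − r²)·√(2/108)) − 1.960).
- Assumed SD 20: the standard error is 20 × 0.1361 = 2.72, and 5/2.72 − 1.96 = −0.12, so power is 45%. With adjustment it is 49% (r = 0.3), 56% (r = 0.5) and 63% (r = 0.6).
- Implied SD 7.03: the standard error is 0.957, and 5/0.957 − 1.96 = 3.27, so power exceeds 99% before adjustment.

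For a wider SD range, with 120 per arm before dropout, going from no adjustment to r = 0.5 moves power from 73% to 85% at SD 15, and from 34% to 43% at SD 25. With 360 per arm at SD 20 it moves from 92% to 97%.

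**The case against.** Four points can be made for the plan, and each has some force.

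First, a reader might infer that the plan ignores baseline TTR. It does not say so. INR is collected at months 3 to 12, so TTR may fall under the mixed model for follow-up data. That model can carry baseline TTR and hospital, and its covariates may be set out in a full protocol or analysis plan not shown here. This stands. What remains is that the article presents two routes for TTR and does not say which is primary.

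Second, a reader might infer that no mean difference would be available if Mann–Whitney were chosen. Arm means and SDs are to be reported in any case, and a difference with its confidence interval can be derived from them. The pre-test governs the P value and the question it answers.

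Third, the rule is written down in advance, and when the arms share one distribution the two-stage procedure keeps its 5% level. A claim of general type I error inflation is therefore unsupported. The 16.5% arises in a constructed case, although unequal spread is plausible for an intervention meant to tighten INR control.

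Fourth, the precision gain is not certain. Eligibility requires expected future warfarin treatment, not past treatment, so new starters may have no TTR for the preceding 12 months. An unadjusted randomised comparison is also valid. Both are true. They reduce the gain but give no reason to forgo it.

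**Conclusion.** The point holds in limited form. The article states a rule under which the effect measure of the primary TTR comparison depends on the observed distribution, the arm size and an unspecified version of the Kolmogorov–Smirnov test. The two tests it names use neither baseline TTR nor hospital, and it does not rank them against the mixed model.

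The cost is an unfixed effect measure and lost precision. The precision part is 9–36% of residual variance among patients with a baseline TTR, if the correlation is 0.3 to 0.6. It should not be read as showing that the SMART versus anticoagulation clinic comparison is underpowered: 45% power rests on an assumed SD of 20, and the article's own n = 31 implies an SD near 7, at which power is not in question. Whether that implied SD is realistic is a separate matter that the article does not settle.

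**What to change.** Drop the normality pre-test for TTR and name one primary analysis: a linear model of 12-month TTR on randomised group, baseline TTR and hospital, with robust standard errors, reported as the adjusted mean difference with its 95% confidence interval. Include a missing-baseline indicator for patients without prior INR tests. Because prior TTR refers to the period before enrolment, its absence cannot be caused by allocation.

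Keep Mann–Whitney, stratified by hospital, as a sensitivity analysis. State that the mixed model is supportive for TTR, or say what it is primary for. Quote any power figure with its assumed SD and correlation.

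The cost is an amendment or analysis plan wording. Hospital is known for every patient and baseline TTR is already in the data collection schedule, so no new data are needed. As recruitment has begun, the change should be dated before any comparison of outcomes by arm.
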